### Sample size calculations

We assume that the outcome measures are continuous variables with a normal distribution, and two independent clinical groups are being compared. Estimates of statistical power are calculated for the primary outcome measure. The neurocognitive tests applied in the study (MCCB battery) are designed for repeated administrations to test possible treatment effects. Some improvement must be expected in both groups because of the treatment/stimulation and as retest effects (being accustomed to the test design if not the actual test material). Nevertheless, we expect that the effect size in the EG will be 0.50 standard deviations (which is a medium effect size) *larger* than the increase in the CSG, which given a statistical power of 0.80 and alpha of 0.05 necessitates a sample size of 55 in each group. The dropout rate in the current study after randomization and group assignment is estimated to 15 %. Thus, the estimate is that recruitment of 126 participants is needed to secure the participation of 55 individuals in each group. Further attrition at later stages in the study progress is accounted for by utilizing the “intention-to treat” analysis.

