### Statistical analysis

Decisions about sample size and design of the project are primarily aimed at comparing the EG with the CSG. The main statistical analyses will be variants of analyses of variance such as Multivariate ANOVA (MANOVA) to test overall group differences, repeated measures ANOVA to look for interactions between time and group (i.e. to test whether the EG have larger change between time points than CSG). Changes in outcome measures will be correlated with changes in CRF. Analysis of covariance will be used to test hypotheses whether the effect of specific variables extend beyond effects of nonspecific variables. Baseline data could be analyzed without referral to later group membership, enabling analyses of empirically derived subgroups such as participants scoring low or high on the physiological measures, or participants with or without concurrent tobacco use. Baseline data will also be analyzed with regression analyses and correlations/partial correlations controlling for potential confounding variables.

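### 55 per group does not follow from the stated inputs: two-sided power for a 0.50 SD difference is about 74%, and 80% would need 64 per group

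*Protocol article*

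**What the plan says.** The Sample size calculations section assumes "continuous variables with a normal distribution, and two independent clinical groups are being compared". It says that power is calculated for the primary outcome (the neurocognitive battery), allows for some retest gain in both arms, and expects the gain in the exercise group to exceed that in the computer gaming group by 0.50 SD. From this it concludes that the difference, "which given a statistical power of 0.80 and alpha of 0.05 necessitates a sample size of 55 in each group".

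The section then allows for 15% dropout and sets recruitment at 126 in order to "secure the participation of 55 individuals in each group". It gives no sidedness, no correlation between baseline and follow-up scores and no adjustment for baseline. It also does not say whether the 0.50 is in SDs of the score or of the change.

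The Statistical analysis section says: "The main statistical analyses will be variants of analyses of variance such as Multivariate ANOVA (MANOVA) to test overall group differences". It adds repeated measures ANOVA for the time-by-group interaction, and mentions analysis of covariance for a separate purpose.

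**The concern.** Effect size, alpha, power, outcome type and group structure are all printed, and together they determine a sample size once sidedness is chosen. The number printed is not the one they determine. This is not a complaint about detail left to a statistical analysis plan: the article states a numerical result that its own inputs do not produce.

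What is at stake is how the result will be read. The Background criticises earlier exercise trials for small samples, and the Discussion foresees that finding no differential improvement would weaken the case for physical activity as a treatment. Readers of a null result will assume that a 0.50 SD effect had an 80% chance of detection. If the chance was nearer 74%, they would give the null result more weight than the design supports.

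**Working it through.** **Inputs, all from Sample size calculations:** difference 0.50 SD (SD = 1), alpha 0.05, power 0.80, two independent normal groups, equal allocation (55 and 55). Sidedness is not stated, so both are tried.

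**Step 1. Try to reproduce 55 per group.** Normal approximation, n per group = 2(z_alpha + z_power)² / d².

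- Two-sided: 2(1.960 + 0.842)² / 0.25 = 62.8, so 63. Exact noncentral t: 63.8, so 64.
- One-sided: 2(1.645 + 0.842)² / 0.25 = 49.5, so 50. Exact noncentral t: 50.2, so 51.

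Neither reading gives 55.

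**Step 2. Power that 55 per group delivers.** Noncentrality = d√(n/2) = 0.50 × √27.5 = 2.622, with 108 degrees of freedom.

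| Test at alpha 0.05, d = 0.50 | n per group | Power (exact t) |
|---|---|---|
| Two-sided | 55 | 73.8% |
| Two-sided | 63 | 79.5% |
| Two-sided | 64 | 80.1% |
| One-sided | 51 | 80.6% |
| One-sided | 55 | 83.2% |

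The normal approximation for 55, two-sided, is 74.6%. The chance of a miss on the exact figure is 100 − 73.8 = 26.2%.

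**Step 3. Difference detectable with 55 per group.** Two-sided alpha 0.05 and 80% power: d = 0.539, about 0.54 SD.

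**Step 4. Which unstated assumption would give 55?** With r the correlation between baseline and end-of-intervention (T1) scores, in score SDs:

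- SD of change = √(2(1 − r)), so the standardised difference for a change-score test is 0.50/√(2(1 − r)).
- Residual SD after adjusting for baseline = √(1 − r²), so for ANCOVA it is 0.50/√(1 − r²).
- If the 0.50 is already in change SDs, a change-score test keeps d = 0.50, and ANCOVA gives 0.50 × √(2/(1 + r)).

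Two-sided at 80% power, 55 per group follows from r of about 0.57 (change score, score SDs), 0.37 to 0.38 (ANCOVA, score SDs; 0.35 by the normal approximation), or 0.70 to 0.72 (ANCOVA, change SDs). None of these correlations appears in the article.

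**Step 5. Power with 55 per group under ANCOVA, two-sided.**

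| r | 0.50 in change SDs | 0.50 in score SDs |
|---|---|---|
| 0.5 | 85% | 85% |
| 0.6 | 83% | 90% |
| 0.7 | 80% | 95% |
| 0.8 | 78% | 99% |

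The range of r is an assumption. At r = 0.3 in score SDs, ANCOVA power is 77.8%.

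**Side note on recruitment.** 126 × 0.85 = 107.1, or 53 to 54 per group rather than 55. Two-sided power there is about 72.7%. This comes from the dropout step and is separate from the error in the 55.

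**The case against.** The strongest reply is that the quantity powered is a difference in gains measured repeatedly, not a difference at one time point. With repeated measures, baseline carries information, and Step 4 shows that a moderate correlation makes 55 exactly right. On that view the 55 is under-documented rather than wrong, and the design may well have 80% power.

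Part of this stands. The true power of the eventual analysis depends on a correlation that the article does not give, so 74% is the power under the inputs as printed, not a fixed property of the trial. But the section describes a plain comparison of independent groups and nothing in it points to a correlation. If the 0.50 is in change SDs, a time-by-group interaction over two time points is a t test on change, and power stays at 73.8%.

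A second reply is that the hypothesis in the Background is directional, and a one-sided 5% test has 83.2% power with 55 per group. That would remove the shortfall, but it still does not yield 55, since 51 would do. No one-sided test is announced, and the planned F tests are non-directional.

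A third reply is that six points of power bias no estimate and leave the type I error unchanged. That is true. The damage is confined to the claim about sensitivity.

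**Conclusion.** The concern holds. The stated 55 per group is not what the printed inputs require under either sidedness: 64 two-sided, 51 one-sided. On the two-sided reading, power is 73.8% rather than 80%, a shortfall of about 6 percentage points. Equivalently, the detectable difference is 0.54 SD rather than 0.50 SD.

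That no plain two-sample test on these inputs gives 55 does not depend on sidedness. The size of the shortfall does: it assumes a two-sided 0.05 t test, no gain from baseline data, and 55 analysed per group. A baseline-adjusted analysis could close the gap, but only with a correlation the article would have to state.

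**What to change.** Correct the paragraph in one of two ways, stating the sidedness and the SD unit in either case.

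1. **Minimum correction.** Keep 55 and report what it delivers. Suggested text: *With 55 participants per group, a two-sided test at alpha 0.05 has 74% power to detect a between-group difference of 0.50 SD [of the score / of the change], and 80% power for 0.54 SD.*
2. **Preferable, though a design choice rather than a correction.** Base the calculation on a baseline-adjusted (ANCOVA) comparison at T1, give the assumed baseline-to-T1 correlation with its source, and make that the primary analysis so that calculation and test agree. The second table in the working shows the resulting power. It reaches 80% with 55 per group in most of the scenarios, but falls just short at r = 0.8 in change SDs and for r below about 0.37 in score SDs.

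The cost is one rewritten paragraph. Option 1 needs no extra patients but makes the stated power less favourable. Option 2 also needs none if the assumed correlation is one that reaches 80%, and it requires a commitment to the adjusted analysis. Holding to the unadjusted two-sided test at 80% power for 0.50 SD would instead mean 64 analysed per group, or 64/0.85 = 75.3, so 76 per group (152 in total) recruited at 15% dropout, against the planned 126.

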## Trial status

The recruitment started August 2014. By April 2015 a total of 32 subjects were participating. Five subjects have dropped out of the study. The planned recruitment of 126 participants will be completed by October 2016.

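### At the stated 15% drop-out, 126 recruits leave about 107 participants, not the 110 (55 per group) that the protocol says they secure

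*Protocol article*

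**What the plan says.** Under Sample size calculations, the protocol article builds the recruitment target in three linked steps.

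- **Number needed.** The expected advantage of the exercise group is 0.50 SD ("we expect that the effect size in the EG will be 0.50 standard deviations" larger than the gain in the comparison group). This, "given a statistical power of 0.80 and alpha of 0.05", "necessitates a sample size of 55 in each group", which makes 110 in total. The text does not say whether alpha is one-sided or two-sided.
- **Loss allowed for.** "The dropout rate in the current study after randomization and group assignment is estimated to 15" per cent. The rate is therefore defined on those already randomized.
- **Recruitment target.** As a consequence, "the estimate is that recruitment of 126 participants is needed to secure the participation of 55 individuals in each group".

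The section then adds that further attrition at later stages is dealt with by the intention-to-treat analysis. Trial status repeats the target: "The planned recruitment of 126 participants will be completed by October 2016". The article does not print the formula that leads from 110 to 126.

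**The concern.** A drop-out rate that applies to those randomized calls for dividing the required number by the retained fraction, here 0.85. Multiplying by one plus the rate gives too small a target, because the loss is then taken from a base larger than the one used to calculate the allowance. The printed 126 looks like the result of that multiplication.

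What is at stake is whether the target does what the text says it does. The article states the number needed, the expected loss, the number to recruit and the claimed result, so the chain can be checked without any further document. If it fails, a trial that recruits exactly to plan and loses exactly the planned share still ends with fewer participants than its power statement assumes.

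**Working it through.** **Inputs**, all from Sample size calculations: 55 per group (110 in total); 15% loss after randomization; 126 recruits; difference 0.50 SD; alpha 0.05. Equal allocation is inferred from the equal group sizes.

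**1. Reproducing the printed figure.**
- Multiplying: 110 × (1 + 0.15) = 126.5, which gives 126 if the fraction is dropped.
- Dividing: 110/(1 − 0.15) = 129.4, which does not give 126.

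The multiplication is thus a plausible source of 126. It remains an inference, and the steps below do not depend on it.

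**2. What 126 delivers at 15% loss.**
- 126 × 0.85 = 107.1 in total, or 107.1/2 = 53.55 per group.
- Shortfall against the stated result: 110 − 107.1 = 2.9, about 3 completers.

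**3. What 55 per group requires at 15% loss.**
- 110/0.85 = 129.4, rounded up to 130 (65 per group).
- Check: 130 × 0.85 = 110.5, which covers 110.
- Difference from the printed target: 130 − 126 = 4 recruits.

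**4. The loss that 126 can absorb.**
- 1 − 110/126 = 0.127, or 12.7%, which is below the stated 15%.

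**5. Effect on power.** Two-sample t-test, difference 0.50 SD, alpha 0.05. Both versions are shown because sidedness is not stated.

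| Per group | Two-sided power | One-sided power |
|---|---|---|
| 55 (claimed) | 73.8% | 83.2% |
| 53.55 (126 recruits, 15% loss) | 72.7% | 82.3% |

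The step costs about 1.2 points two-sided and 0.9 points one-sided. The difference detectable with 80% two-sided power moves from 0.539 to 0.546 SD.

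**6. Separating this from the other shortfall.** Two-sided, 55 per group already falls 80 − 73.8 = 6.2 points short of the stated 80%. The t-test needs 64 per group. Of the full gap at 53.55 per group, 80 − 72.7 = 7.3 points, only about 1.2 come from the drop-out step.

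**The case against.** The strongest objection concerns size. Four recruits and about one point of power change no design choice, and no conclusion would turn on them. That stands, and it sets the grade: this is a minor correction.

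A second defence is that the intention-to-treat analysis covers the loss. It does not reach this step. The article assigns that analysis to further attrition at later stages, whereas the 15% is the separate loss that the 126 is meant to absorb.

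A third is that the source of 126 is not documented. This is correct: 126.5 has to be cut down rather than rounded up to give 126, and 126 is also 2 × 63, the uninflated two-sided total for 0.50 SD under the normal approximation. Whichever route was taken, 126 recruits do not leave 55 per group at 15% loss.

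Three stronger readings are tempting, and the document supports none of them.

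- *The trial's own losses already show that 15% is too low.* Trial status reports 32 subjects participating by April 2015 and says "Five subjects have dropped out of the study". It does not say whether the five are among the 32 (5/32 = 15.6%) or additional to them (5/37 = 13.5%), nor whether they left before or after randomization. Counts this small neither confirm nor refute 15%.
- *Loss could approach the 38% that the Background reports for an earlier exercise study.* That study ran for 6 months. This intervention lasts 12 weeks and includes transport and motivational support. The figure has no bearing on whether 126 follows from 110 and 15%.
- *The drop-out step brings power down to about 73%.* Nearly all of that gap comes from the 55 per group. If the test were one-sided, power would still be 82.3% after the loss. A one-sided test does not explain the 55 either, since it needs about 51 per group.

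**Conclusion.** The point holds as a minor arithmetic error, wrong as written. The required number, the drop-out rate and the recruitment target cannot all be correct together: at 15% loss 126 recruits leave about 107 participants, and 110 would need 130. The error runs in the unfavourable direction, and nothing elsewhere in the article corrects it.

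The conclusion rests on reading the 15% as a share of those randomized, which is how the article defines it, and on equal allocation. It does not rest on how 126 was obtained. The power figures also assume a two-sample t-test at 0.50 SD, with the sidedness given beside each. The shortfall of 55 per group against 80% two-sided power is a separate and larger matter and should not be counted here.

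**What to change.** In Sample size calculations, make one of these two changes:

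- state that 126 recruits are expected to yield about 107 completers (53 to 54 per group) at 15% loss, and give the matching power with its sidedness (72.7% two-sided or 82.3% one-sided at 0.50 SD); or
- state that 126 secures 55 per group only if loss is 12.7% or less.

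In either case, note that 130 is the number that secures 55 per group at 15% loss.

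The cost is wording only, with slightly less favourable figures for completers and power. Choosing to recruit 130 would add 4 participants, but would not by itself reach 80% two-sided power, because 55 per group gives 73.8%. If that number is revised as well, the division by 0.85 should be applied to the revised total: 64 per group would need 128/0.85 = 150.6, so 151.

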### Protocol deviations

When absent from scheduled exercise or computer gaming, the participant will be contacted and offered to participate on a following day the same week. Participants who fail to complete at least 60 % of the total number of intervention sessions or have not participated for more than 2 successive weeks are considered protocol violators. Participants who are unable to meet for the VO_2max_ test within 10 days following the last training session will also be considered protocol violators. However, they will be allowed to stay in the study and will be tested as soon as possible, as well as invited to take part in T_2_. Statistical analyses will be performed both based on the principle of “intention-to-treat” including everyone regardless of protocol violations, but “per protocol” analyses will also be executed, comparing only those who completed the two treatment conditions according to the protocol.

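### Intention-to-treat does not account for attrition, and the MANOVA and repeated measures ANOVA named for the main analysis drop incomplete cases unless a missing-data method is added

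*Protocol article*

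**What the plan says.** Three sections of the protocol article bear on this.

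- **Sample size calculations.** The comparison is of two independent groups. The planned effect is given as "we expect that the effect size in the EG will be 0.50 standard deviations" above the gain in the comparison group, and "given a statistical power of 0.80 and alpha of 0.05 necessitates a sample size of 55 in each group". Dropout is then added: "The dropout rate in the current study after randomization and group assignment is estimated to 15" per cent, which leads to a target of 126 recruited "to secure the participation of 55 individuals in each group". Loss beyond that gets no rate. The text says only: "Further attrition at later stages in the study progress is accounted for by utilizing the" intention-to-treat analysis.
- **Protocol deviations.** Intention-to-treat is described as "including everyone regardless of protocol violations". The violations listed are low attendance, a gap of more than two weeks, and a late fitness test. Violators stay in the study and are still assessed. A per-protocol analysis is listed separately.
- **Statistical analysis.** The main analyses are variants of analysis of variance. The examples given are MANOVA for overall group differences and "repeated measures ANOVA to look for interactions between time and group".

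The Assessments section sets outcomes at baseline (T0), 12 weeks (T1) and 28 weeks (T2), and defines change from T0 to T1 and from T1 to T2. The article names no imputation or likelihood-based method, and nowhere says that incomplete participants are excluded.

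**The concern.** An article may leave its missing-data method to an analysis plan, and silence would not be a fault. This article is not silent. It names a remedy for attrition, relies on it in the sample-size argument, and the remedy does not do what is claimed. Intention-to-treat settles who belongs to which arm. A participant with no T1 score still has no T1 score after being assigned to the right arm.

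The named methods do not close the gap. In standard form, MANOVA and repeated measures ANOVA need a value for every variable in the model and omit anyone who lacks one.

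Power is one stake. Bias is the other: the Discussion calls adherence to the exercise regime perhaps the greatest challenge, so dropout may differ between arms in number and in kind. The Background lists failure to analyse by intention-to-treat among the common limitations of earlier trials, and the article says this trial addresses them. It also cites a trial with 38% attrition whose per-protocol effects were not seen under intention-to-treat.

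**Working it through.** **1. What each model keeps.** Standard-form methods, no imputation:

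| Model | Omitted | Kept |
|---|---|---|
| T0 and T1 only | anyone missing T1 | anyone with T0 and T1, even if T2 is missing |
| T0, T1 and T2 | anyone missing T1 or T2 | only those seen at all three visits |

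Neither model includes everyone once a score is missing. Protocol violators who attend the assessments stay in both.

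**2. Inputs.** From Sample size calculations: difference d = 0.50 SD, alpha 0.05, target power 0.80, 55 per group, 15% dropout, 126 recruited. Assumptions of this check: a two-sided test (sidedness is not stated), equal allocation, equal loss in both arms, and the 15% falling before T1.

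**3. The plan's own figures.** Power by the normal approximation is Φ(d√(n/2) − 1.96). With n = 55: 0.50 × √27.5 = 2.622, and Φ(0.662) = 0.746. The exact t-test gives 0.74. So 55 per group falls short of 0.80 before any loss; the two-sided t-test needs 64 per group. This is a separate issue, noted here so that its share of the gap is not charged to attrition.

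**4. Reserve for later loss.** 126 × (1 − 0.15) = 107.1, against 2 × 55 = 110. The planned 15% alone takes the trial just below its own target. The figure 126 is close to 110 × 1.15 = 126.5, whereas 110 / 0.85 = 129.4 would call for 130.

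**5. Complete-case power.** n per arm = 126 × (1 − total loss) / 2.

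| Total loss | n per arm | d√(n/2) | Power, normal | Power, t-test |
|---|---|---|---|---|
| 15% (planned) | 53.6 | 2.587 | 0.735 | 0.73 |
| 25% (assumed) | 47.3 | 2.430 | 0.681 | 0.67 |
| 38% (assumed) | 39.1 | 2.210 | 0.599 | 0.59 |

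The 15% row fits a T0–T1 model. The other rows fit a three-visit model with a further 10 or 23 percentage points lost by T2. The 38% is the attrition of the trial cited in the Background, used here as an upper bound. A one-sided test would give 0.82, 0.78 and 0.71.

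**6. What is attributable.** Of the fall from 0.80, the step to 0.74 comes from the sample size itself, and the step to 0.73 comes from the planned dropout not being fully covered by 126. The later attrition that the sentence claims to cover accounts for the drop from 0.73 to between 0.67 and 0.59, and only in a three-visit model.

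**The case against.** The strongest reply is that the sentence is loose wording and the rest is detail left to a plan not shown. The list of methods is open, so ANOVA after imputation or a likelihood-based variant would fit it. The phrase about including everyone concerns protocol violations, not missing outcomes. Much of this stands, and it rules out several stronger readings:

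- A reader might infer that the trial plans a completer analysis. It does not: violators who attend assessments are included, and per protocol is separate. Complete-case for the visits in each model is the accurate description.
- A reader might infer that anyone missing only T2 is lost from the T0–T1 comparison as well. That holds only for a single three-visit model. The article defines the two changes separately and does not fix such a model.
- A reader might infer that the intention-to-treat rule and the named methods cannot coexist. They can, if a missing-data method is added.
- A reader might attribute the whole gap from 0.80 to attrition, or put a figure on the bias. The first ignores the sample-size shortfall. For the second, the article gives no loss by arm and no link between loss and scores, so any figure would come from invented inputs.

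The assumed rates may also prove too high. The Trial status section reports 32 participating and five dropouts, that is 5/37 = 14% or 5/32 = 16% depending on whether the 32 include the five. That is close to the planned 15%, although it is an early count and says little about loss by T2.

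What the reply does not rescue is the sentence itself. It asserts that attrition is dealt with, and neither the principle cited nor the methods named deal with it. Even a T0–T1 model omits everyone without a T1 score.

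**Conclusion.** The concern holds in this form: the article wrongly says that attrition beyond 15% is covered by intention-to-treat, and its named main analyses, run in standard form, are complete-case and so do not deliver the inclusive analysis described under Protocol deviations. The sections fit together only if a missing-data method is added.

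The error in the sentence rests on no assumption. The size does. The sample has no reserve (107 against 110). Two-sided power is about 0.73 at the planned loss, and about 0.67 to 0.59 if a three-visit model is used and total loss is 25% to 38%. Those two rates are illustrative, since the protocol gives none for later loss. Bias from unequal dropout is plausible, but its size cannot be derived from the document.

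**What to change.** - Delete the sentence saying that intention-to-treat accounts for further attrition. State instead that intention-to-treat means analysis of all randomised participants as allocated, and describe the handling of missing scores separately.
- Replace MANOVA and repeated measures ANOVA as the main analysis with a likelihood-based linear mixed model: all randomised participants as allocated, all observed T0, T1 and T2 scores, and visit-by-arm terms. An observed T1 score then counts whether or not T2 is present.
- Add one sensitivity analysis for data missing not at random, for example a shift applied to the unobserved scores of dropouts in the exercise arm over a stated range.

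**Cost.** Changed wording and slightly more analysis work. SPSS, already named in the article, fits such models, and no new data are needed. The main result would rest on a missing-at-random assumption, which is why the sensitivity analysis belongs with it. The model makes use of scores that were observed; it does not recover the information in T1 scores never collected, and it does not mend the separate sample-size shortfall. Imputation before the planned ANOVA would be an acceptable alternative if specified in advance.
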